**Details of the proposed investigation**

1. **Title**: **A PROSPECTIVE, RANDOMIZED, CONTROLLED EVALUATION OF THE EFFECTS OF OPTIMISATION OF CEREBRAL OXYGENATION AND DEPTH OF ANAESTHESIA ON POSTOPERATIVE COGNITIVE DYSFUNCTION IN ELDERLY PATIENTS UNDERGOING MAJOR ORTHOPAEDIC AND ABDOMINAL SURGERY**

2. **Research objectives**: The current proposal will determine the frequency and importance of Post-Operative Cognitive Decline (POCD) in older people (over the age of 65), determine the subsequent incidence of Mild Cognitive Impairment and dementia and evaluate the role of key peri-operative intervention strategies and biological risk factors which will enable the development and implementation of preventative therapeutic strategies.

3. **Background**: Clinical experience has always suggested that older people often develop impairments of cognitive function after major surgical interventions. It is however only over the last decade that systematic studies have investigated the problem, coining the term Postoperative cognitive decline (POCD). This body of work has highlighted the frequency and importance of POCD, which has become increasingly recognized as a common and potentially handicapping outcome after a broad range of major surgical procedures. Although there is some variability between reports, probably reflecting the individual study definitions of POCD and the differing age range of participants, the mean reported incidence rates are 25% (range 7 - 55%) at 1 week post-operatively and 10% (range 7-15%) at 3 months post-operatively for non-cardiac procedures. These findings clearly indicate that POCD is a frequent and often persistent syndrome at all ages.

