Other candidate genetic factors which may increase vulnerability to POCD include polymorphisms that increase risk of dementia (eg APOE4) and polymorphisms associated with delirium (eg NMDAR1 G2108A polymorphism, an insertion/deletion polymorphism in the promoter region NQO2 and a variable number of tandem repeats (VNTR) polymorphism in the 3’ non-coding region of the dopamine transporter DAT in patients with a history of delirium tremens during alcohol withdrawal). It is also possible that other genetic factors may be protective, for example a common candidate polymorphism that is associated with improved attentional performance may reduce the risk of POCD (BuChE K variant). We therefore hypothesise that particular individuals could be at greater risk of POCD based upon genetic vulnerability; and that there may be an interaction of peri-operative circumstances and individual biological vulnerability. Identifying key risk factors will enable individuals at particularly high risk to be identified, so that strategies can be employed to minimize the risk; and both risk and protective factors will give important insights into the mechanisms of POCD which will enable the development of more effective treatments and better prevention.

By addressing these key questions, the current proposal will clarify the full importance of POCD in people over the age of 70, determine the incidence of subsequent MCI and dementia and examine the impact of a an intra-operative intervention to prevent post operative cognitive dysfunction.

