**7. Hypotheses**

a)In an RCT, closer anaesthetic monitoring and anaesthetic management of patients during surgery will improve post-operative cognitive outcomes compared with patients receiving usual anaesthetic monitoring at 7 days and at 3 months post-operatively.

.

b)Twelve months post-operatively, overall cognitive performance and function on every day activities will be significantly more impaired in post-operative patients than in age matched controls.

c) Twelve months post-operatively the incidence of MCI and dementia will be significantly higher in post-operative patients than in age matched controls.

d) A fall in cerebral oxygenation >15% will be associated with a significant increase in the risk of POCD and strategies to correct or minimise this fall with reduce the incidence of POCD

e) Minimisation of cumulative deep anaesthetic time will reduce the incidence of POCD

f) Genes predisposing to dementia, attentional impairments, delirium and abnormal NOS activity will increase the risk of POCD.

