**8** **Methods** **Participants, Inclusion and exclusion criteria**:

*Randomized Controlled Trial (RCT)*

One hundred patients, 60 years of age and older, with an American Society of Anesthesiologists (ASA) classification of fitness of 3 or less, undergoing major elective abdominal or orthopaedic surgery under general anaesthesia at King’s College Hospital will participate in the study.

Inclusion criteria

(1)Patients over 60 years of age classified as ASA (American Society of Anesthesiologists) of three or less who were due to undergo major elective abdominal or orthopaedic surgery (2) Mini Mental State Examination (MMSE) score equal to or greater than 23. (3) Adequate English was a pre-requisite to enable consent and to undertake study assessments.

Exclusion criteria

(1) Unable to complete the outcome measures (2) A diagnosis of Alzheimer’s disease or other dementia (3) Individuals undergoing surgical procedures under regional anaesthetics.

Assessments

1/ Electrocardiography (ECG) and laboratory tests as clinically indicated.

2/ Cognitive evaluation: Global cognitive function (Cambridge Assessment for Mental Disorder in the Elderly, section B (CAMCOG-B - , Mini-Mental State Examination -MMSE), memory (CAMCOG memory subscale), executive function (Trail – Making task part A and B) and vigilance accuracy and vigilance reaction time from the Cognitive Drug Research battery as indices of attentional performance and cognitive processing speed pre-operatively, 1 week post surgery and 12 weeks post surgery.

Definitions of POCD and other criteria for cognitive dysfunction will be validated based upon an initial cohort study (appendix 1).

Randomisation

Participants will be randomized according torandomisation lists, stratified by age group (65 to 70, 70 to 75 and over 75) , which will be generated by the study statistician in the statistical program package R. Based upon the list, sealed envelopes containing the randomization codes will be delivered to the operating theatres, and an envelope selected randomly by the anaesthetist. The randomisation envelope will be opened only after the participant’s eligibility and willingness to participate are re-confirmed prior to surgery.

Blinding

The trial will be double blind with the patients, informants and researchers blind to treatment allocation.

Monitoring and Intervention

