A bispectral index (BIS) of the electroencephalogram will be used to monitor anaesthetic depth. The target BIS range will be 40-60 (±5).

During and until extubation after the procedure, rSO2 will be continuously monitored using SICO to enable interventions if regional cerebral saturations drop by more than 15% from baseline or to less than 50% intraoperatively, using the following algorithm

1. BP maintained within 10% of baseline value by giving fluids or inotropes to bring the value back to within these limits
2. SpO2 maintained above 95% by increasing the FIO2 to 50%
3. Maintain EtCO2 between 4·5 to 5·5%. avoiding excessive hypercarbia as well as hypocarbia.
4. If there is ongoing moderate to severe haemorrhage consider transfusion if the Hb level is less than 9g.dl-1

If all the above fail to correct a decline then increase the etCO2 to 6% and give 100% O2.

Intervention

In the intervention group the anaesthetist will have full access to the BIS and SICO data to optimize the depth of anesthesia and to identify and facilitate intervention to rectify cerebral oxygen desaturation. In the control group the BIS and SICO data will be collected, but the anaesthetist will be blind to the monitoring data.

Statistical methods

The study is powered as a pilot study. A cohort of 73 patients gives 80% power to the 5% level of significance to detect a between group difference of 0·33 SD. The goal is to enroll 100 participants to allow for drop-outs.

The primary efficacy population will be defined as all patients who were randomised to receive the intra-operative anesthetic intervention or treatment as usual and completed at least one follow-up assessment. Statistical analyses will be undertaken using the SPSS software, version 17.0 (SPSS, Chicago, IL, USA). Two-sided p values of less than 0·05 will be deemed to be statistically significant. A full statistical evaluation protocol will be developed by the study statistician.

Additional Objectives

Fifty age matched controls will be recruited in parallel, drawn from the spouses of people undergoing surgery. The pre-operative assessment will include a standardized evaluation to identify pre-existing delirium (Confusion Assessment Method CAM29) or significant cognitive impairment including MMSE <2530, and/or the presence of dementia (DSMIIIR criteria, American Psychiatric Association 1987). This will allow additional comparisons between post-operative patients and age matched controls to address hypotheses b-f.

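### Hypotheses b and c are set at twelve months, but the written schedule ends at 12 weeks, gives the controls no follow-up visit, and names no measure of everyday function and no post-operative assessment of MCI or dementia

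*Protocol*

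**What the plan says.** Section 7 lists six hypotheses, a to f. Two are set one year after surgery and compare patients with non-surgical controls. Hypothesis b begins "Twelve months post-operatively, overall cognitive performance and function on every day activities will be significantly more impaired", and hypothesis c reads "Twelve months post-operatively the incidence of MCI and dementia will be significantly higher in post-operative patients than in age matched controls".

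Section 2 makes it a research objective to "determine the subsequent incidence of Mild Cognitive Impairment and dementia". The end of section 6 repeats the aim: "determine the incidence of subsequent MCI and dementia". Neither statement gives a time point.

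In section 8 the list of cognitive tests under Assessments closes with their timing: "cognitive processing speed pre-operatively, 1 week post surgery and 12 weeks post surgery". No later visit is written anywhere in the protocol.

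The controls appear only under Additional Objectives in section 8: "Fifty age matched controls will be recruited in parallel, drawn from the spouses of people undergoing surgery". That paragraph goes on to describe a pre-operative evaluation for delirium, low MMSE and dementia, and concludes: "This will allow additional comparisons between post-operative patients and age matched controls to address hypotheses b-f".

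**The concern.** A hypothesis about status or incidence at twelve months needs an observation at twelve months in both groups, and an instrument that records the outcome. The protocol says that recruiting the controls is enough to address b to f, yet for b and c it writes neither the visit nor the instrument.

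This cannot be left to a statistical analysis plan. Such a plan can define an endpoint from data in hand, but it cannot analyse a visit that was never made, and a missed visit cannot be recovered later. Fifty controls would be enrolled for comparisons that the study, run as written, could not make. One of the stated objectives would go unanswered.

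**Working it through.** No sample-size or power figure is involved. The check sets what each statement needs beside what the protocol schedules.

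| Statement | Time point | Needs | Written in section 8 |
|---|---|---|---|
| Hypothesis a (randomised comparison) | 7 days and 3 months | Cognitive battery in patients | Battery at 1 week and 12 weeks: covered |
| Hypothesis b, cognition | 12 months | Cognitive battery, patients and controls | Patients: last test at 12 weeks. Controls: no post-baseline test stated |
| Hypothesis b, everyday function | 12 months | A functional measure, patients and controls | No functional measure named |
| Hypothesis c | 12 months | Baseline status, then MCI and dementia assessment, patients and controls | Dementia criteria named only for the pre-operative evaluation; no MCI assessment named |
| Objective in sections 2 and 6 | None given | Post-operative MCI and dementia assessment at some time | None named at any time |

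**Timing.** Twelve months is about 52 weeks and the last written assessment is at 12 weeks, so the gap is 52 − 12 = 40 weeks. The blood samples, at baseline and one day after surgery, do not extend follow-up.

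**Counts.** Scheduled 12-month observations: 0 of 100 patients and 0 of 50 controls. Stated post-baseline observations in controls: 0.

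**Instruments.** The battery in section 8 covers global cognition, memory, executive function and attention. The reference list contains a paper on an activities-of-daily-living scale and one on MCI, but the Methods cite neither. Nothing in the Methods turns them into planned assessments.

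**Other 12-month data.** Section 3 and Appendix 1 report twelve-month recovery figures. They come from the group's earlier cohort of 100 patients, with no control comparison and no MCI or dementia outcome reported, so they cannot stand in for the missing visit.

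**The case against.** The strongest reply is that the 12-week schedule stands under the randomised-trial heading and fits hypothesis a exactly: "compared with patients receiving usual anaesthetic monitoring at 7 days and at 3 months post-operatively". The comparison with controls belongs to the Additional Objectives, which might have been meant to follow a schedule of their own. That is possible, but none is written, and the place where it would stand instead says that the comparisons are already provided for.

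A second reply is that section 8 promises definitions of cognitive dysfunction validated on the earlier cohort, and that global tests are given at 12 weeks. A definition can indeed come later. Appendix 1, however, deals with recovery of MMSE and reaction times and mentions neither MCI nor dementia, and no definition supplies a visit.

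A third is that the text at hand is incomplete. Section 6 refers to an appendix 3 that is not in it. That reference concerns a genetic polymorphism, and nothing in the available text points to a visit schedule elsewhere. The conclusion still assumes that there is none.

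Some of the case against stands. The pre-operative evaluation may describe the patients alone, since spouses have no operation. The safe statement is that no control follow-up is written, not that the controls are limited to baseline. The objective in sections 2 and 6 has no time point of its own, so it fails for want of an assessment rather than for want of a 12-month visit.

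**Conclusion.** The mismatch is real. As written, hypotheses b and c (two of six) and the objective on MCI and dementia incidence cannot be tested: no 12-month observation is planned in either group, no follow-up visit is stated for the controls, and the outcome assessments are not named. It should be corrected, but it does not threaten the trial's main question. Hypothesis a is fully scheduled, and the comparison that fails is a non-randomised, additional one in a study described as a pilot.

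A reader might go further and infer from Table 1 in Appendix 1 that 12-week scores, used in place of 12-month ones, would overstate lasting impairment. There, the share of patients not back to baseline on choice reaction time falls from 100 − 68 = 32% at 3 months to 100 − 77 = 23% at 12 months. The documents do not support that inference:

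- The protocol never proposes the substitution.
- Choice and simple reaction time are not in the section 8 battery. On MMSE, the one shared measure, the change is from 100 − 91 = 9% to 100 − 92 = 8%.
- The table has no controls, so it cannot show bias in a comparison of patients with controls.
- Incident MCI and dementia accumulate over time, so an early count would, if anything, miss cases.

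**What to change.** **Low-cost route.**
- Restate hypothesis b as a 12-week cognitive comparison.
- Delete its everyday-function clause, or name a measure and collect it in both groups.
- Write into section 8 that the controls take the same battery as the patients, at baseline and at the same intervals.
- Withdraw hypothesis c and the incidence aim in section 2 and at the end of section 6. Bring the Synopsis and section 9, which lean on that aim, into line.
- Limit the Additional Objectives sentence to the hypotheses that the controls can serve.

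The cost is an amendment, a narrower claim, and control testing at 1 and 12 weeks: at most 50 × 2 = 100 sessions, plus the baseline battery.

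**If the 12-month claims are kept.** Write a 12-month visit for both groups into section 8, with a named measure of everyday function and a named MCI and dementia assessment, the latter also given at baseline so that incident cases can be told from existing ones. The cost is up to 100 + 50 = 150 further visits before losses, plus the added instruments.

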**8** **Methods** **Participants, Inclusion and exclusion criteria**:

*Randomized Controlled Trial (RCT)*

One hundred patients, 60 years of age and older, with an American Society of Anesthesiologists (ASA) classification of fitness of 3 or less, undergoing major elective abdominal or orthopaedic surgery under general anaesthesia at King’s College Hospital will participate in the study.

Inclusion criteria

(1)Patients over 60 years of age classified as ASA (American Society of Anesthesiologists) of three or less who were due to undergo major elective abdominal or orthopaedic surgery (2) Mini Mental State Examination (MMSE) score equal to or greater than 23. (3) Adequate English was a pre-requisite to enable consent and to undertake study assessments.

Exclusion criteria

(1) Unable to complete the outcome measures (2) A diagnosis of Alzheimer’s disease or other dementia (3) Individuals undergoing surgical procedures under regional anaesthetics.

Assessments

1/ Electrocardiography (ECG) and laboratory tests as clinically indicated.

2/ Cognitive evaluation: Global cognitive function (Cambridge Assessment for Mental Disorder in the Elderly, section B (CAMCOG-B - , Mini-Mental State Examination -MMSE), memory (CAMCOG memory subscale), executive function (Trail – Making task part A and B) and vigilance accuracy and vigilance reaction time from the Cognitive Drug Research battery as indices of attentional performance and cognitive processing speed pre-operatively, 1 week post surgery and 12 weeks post surgery.

Definitions of POCD and other criteria for cognitive dysfunction will be validated based upon an initial cohort study (appendix 1).

Randomisation

Participants will be randomized according torandomisation lists, stratified by age group (65 to 70, 70 to 75 and over 75) , which will be generated by the study statistician in the statistical program package R. Based upon the list, sealed envelopes containing the randomization codes will be delivered to the operating theatres, and an envelope selected randomly by the anaesthetist. The randomisation envelope will be opened only after the participant’s eligibility and willingness to participate are re-confirmed prior to surgery.

Blinding

The trial will be double blind with the patients, informants and researchers blind to treatment allocation.

Monitoring and Intervention

A bispectral index (BIS) of the electroencephalogram will be used to monitor anaesthetic depth. The target BIS range will be 40-60 (±5).

During and until extubation after the procedure, rSO2 will be continuously monitored using SICO to enable interventions if regional cerebral saturations drop by more than 15% from baseline or to less than 50% intraoperatively, using the following algorithm

1. BP maintained within 10% of baseline value by giving fluids or inotropes to bring the value back to within these limits
2. SpO2 maintained above 95% by increasing the FIO2 to 50%
3. Maintain EtCO2 between 4·5 to 5·5%. avoiding excessive hypercarbia as well as hypocarbia.
4. If there is ongoing moderate to severe haemorrhage consider transfusion if the Hb level is less than 9g.dl-1

If all the above fail to correct a decline then increase the etCO2 to 6% and give 100% O2.

Intervention

In the intervention group the anaesthetist will have full access to the BIS and SICO data to optimize the depth of anesthesia and to identify and facilitate intervention to rectify cerebral oxygen desaturation. In the control group the BIS and SICO data will be collected, but the anaesthetist will be blind to the monitoring data.

Statistical methods

The study is powered as a pilot study. A cohort of 73 patients gives 80% power to the 5% level of significance to detect a between group difference of 0·33 SD. The goal is to enroll 100 participants to allow for drop-outs.

The primary efficacy population will be defined as all patients who were randomised to receive the intra-operative anesthetic intervention or treatment as usual and completed at least one follow-up assessment. Statistical analyses will be undertaken using the SPSS software, version 17.0 (SPSS, Chicago, IL, USA). Two-sided p values of less than 0·05 will be deemed to be statistically significant. A full statistical evaluation protocol will be developed by the study statistician.

Additional Objectives

Fifty age matched controls will be recruited in parallel, drawn from the spouses of people undergoing surgery. The pre-operative assessment will include a standardized evaluation to identify pre-existing delirium (Confusion Assessment Method CAM29) or significant cognitive impairment including MMSE <2530, and/or the presence of dementia (DSMIIIR criteria, American Psychiatric Association 1987). This will allow additional comparisons between post-operative patients and age matched controls to address hypotheses b-f.

As a biomarker of brain injury,26 S100B protein will measured in plasma. Blood samples will be taken from participants at baseline and one day post-surgery. Blood will be collected into K2-EDTA vacutainers and centrifuged at 2,000g for ten minutes. Plasma will be collected and frozen until analysis. S100B concentrations will be measured using a commercially available ELISA (Alpco Diagnostics , Salem, NH, USA) according to the manufacturer’s instructions. A full biomarker analysis protocol will be developed as part of the study.

**9.** **The value of the research to Public health and patient care**: It is clear that Post-Operative Cognitive Decline (POCD) is frequent after major surgical procedures, especially in the oldest age groups. Surprisingly, despite the high incidence rates, awareness is low amongst the medical community and amongst surgical patients; and people are rarely informed of the risk of POCD as part of the consent procedure. Determining the full significance of POCD with respect to longer term cognitive outcomes such as Mild Cognitive Impairment and dementia is essential to enable clear communication of the likely risks and prognosis. Even more importantly elucidating the key contributing factors and the underlying mechanisms is essential so that effective prevention strategies can be assessed.

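### Patients are eligible at MMSE 23 or more, but the screen described with the spouse controls counts MMSE below 25 as significant impairment, and the protocol does not say whom it covers or whether it excludes.

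*Protocol*

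**What the plan says.** **Patients.** Protocol section 8, Inclusion criteria, requires "Mini Mental State Examination (MMSE) score equal to or greater than 23". On dementia, the exclusion list names "A diagnosis of Alzheimer’s disease or other dementia", that is, a diagnosis already made. It sets no upper bound on impairment beyond the MMSE criterion and does not mention a cut-off of 25.

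**Controls and the screen.** Under Additional Objectives in the same section: "Fifty age matched controls will be recruited in parallel, drawn from the spouses of people undergoing surgery". The next sentence reads "The pre-operative assessment will include a standardized evaluation to identify pre-existing delirium" and goes on to "significant cognitive impairment including MMSE <2530, and/or the presence of dementia", with delirium assessed by the Confusion Assessment Method and dementia by DSM-III-R criteria. The 30 after the cut-off is a citation: reference 30 is the MMSE paper, and the Confusion Assessment Method carries its reference number 29 in the same way.

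**Use.** The paragraph ends: "This will allow additional comparisons between post-operative patients and age matched controls to address hypotheses b-f". Section 7 gives the direction of hypothesis b: at 12 months, cognition and everyday function "will be significantly more impaired in post-operative patients than in age matched controls". Hypothesis c predicts more MCI and dementia in patients than in controls at the same time point.

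**The concern.** The same score has two meanings within one section. A patient at 23 or 24 satisfies the entry rule and also meets the protocol's own description of significant cognitive impairment. No other part of the protocol reconciles the two.

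The conflict matters because of where the second threshold appears. It stands with the spouse controls and is said to serve the patient-control comparisons. Those comparisons are not randomised, so nothing in the design balances a difference in how the two groups were admitted. If the entry bar is higher for controls, patients start lower on cognition, which is the direction that hypotheses b and c predict for the effect of surgery. Hypothesis c is also exposed because people close to an impairment threshold at entry are plausible candidates for a later MCI or dementia classification.

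**Working it through.** **Step 1. The overlap.** Eligible patients score 23 or more; significant impairment is a score below 25. Both hold for 23 and 24, a band of two points.

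**Step 2. What each reading of the screen implies.**

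| Reading | Consequence |
|---|---|
| Excludes controls, not patients | People at 23-24 remain only among patients; selection favours hypotheses b and c |
| Excludes patients | Contradicts the inclusion criterion |
| Excludes neither, only records | Eligible patients are labelled significantly impaired with no stated handling; controls have no stated cognitive entry criterion |
| Same exclusion in both groups | No differential selection, but still contradicts the inclusion criterion |

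The dementia rules differ in a similar way: an existing diagnosis for patients, against an assessment by DSM-III-R criteria in the screen.

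**Step 3. Size under the first reading.** The protocol gives no MMSE distribution and no figure for this comparison, so there is nothing to reproduce. As an illustration, draw patients and controls from one normal distribution rounded to whole scores and capped at 30. Keep patients at 23 or more and controls at 25 or more, and assume no effect of surgery.

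Let p be the share of patients at 23-24. Then

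gap = p × (mean of those at 25 or more − mean of those at 23-24),

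and the gap in SD units divides by the root mean square of the two group SDs.

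Central case, assumed mean 27 and SD 2: p = 0.095, the mean at 25 or more is 27.35, and the mean at 23-24 is 23.70. Gap = 0.095 × (27.35 − 23.70) = 0.35 points. The group SDs after truncation are 1.83 and 1.55, so the divisor is √((1.83² + 1.55²)/2) = 1.70 and the gap is 0.20 SD.

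| Assumed mean | Assumed SD | Patients at 23-24 | Gap, points | Gap, SD |
|---|---|---|---|---|
| 26 | 1.5 | 15.0% | 0.41 | 0.30 |
| 26 | 2.0 | 19.4% | 0.61 | 0.37 |
| 26 | 2.5 | 21.0% | 0.73 | 0.40 |
| 27 | 1.5 | 4.7% | 0.15 | 0.11 |
| 27 | 2.0 | 9.5% | 0.35 | 0.20 |
| 27 | 2.5 | 12.7% | 0.50 | 0.27 |
| 28 | 1.5 | 1.0% | 0.04 | 0.03 |
| 28 | 2.0 | 3.7% | 0.16 | 0.10 |
| 28 | 2.5 | 6.8% | 0.30 | 0.16 |

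**Step 4. With one common threshold.** Both groups are then cut at the same score, so their means coincide and the gap from selection is 0 in every row.

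These gaps are on raw MMSE at entry. How much carries through to the 12-month outcomes in hypotheses b and c depends on the outcome and the analysis, which the protocol does not fix.

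**The case against.** The strongest reply is that the text never says the screen excludes anyone. It speaks of a pre-operative assessment, and spouses have no operation, so it may mean the patients, or both groups. Its stated purpose is to identify impairment, and no exclusion rule for controls appears anywhere. A patient at 23 or 24 can be eligible and also be recorded as impaired at baseline; an analysis of incident MCI and dementia would need such a classification. On that reading there is no differential selection. This stands: the bias is conditional, and a reader who infers that the protocol demonstrably screens out controls at 23-24 while keeping such patients goes beyond the text. What remains is that the protocol does not settle the reading, and that the recording-only reading leaves controls without any stated cognitive entry criterion.

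Two further limits also stand. The magnitudes rest on assumed distributions and on raw MMSE at entry, while hypotheses b and c concern 12-month outcomes; an analysis of change from baseline, or one adjusted for baseline, would reduce the effect. And these are additional objectives of a study powered as a pilot.

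A reader might also infer that pooling the two randomised arms against the controls adds to the bias. It would not. If the intervention protects cognition, pooling makes patients look better and shrinks the patient-control gap, away from the hypothesised result. Nor does the protocol say that the arms will be pooled without a term for arm.

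It may be said that all this can wait for the analysis plan. Covariate adjustment can. Eligibility and the screening of controls cannot: an analysis plan written later cannot restore spouses who were never enrolled.

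**Conclusion.** The concern holds as an unreconciled contradiction with a possible selection bias behind it. The overlap at 23-24 follows directly from the two stated thresholds and needs no assumption. The bias towards hypotheses b and c arises only if the screen removes controls and not patients. In that case its size on raw MMSE is 0.03 to 0.40 SD (0.04 to 0.73 points) for assumed means of 26 to 28 and SDs of 1.5 to 2.5, with 0.20 SD in the central case and a negligible amount at the low end.

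The documents do not support a numerical estimate of spurious MCI or dementia incidence, because they give neither the share of patients at 23-24 nor the risk in that band. The randomised comparison in hypothesis a is not affected, since both arms enter under the same rule. The point should be settled before controls are enrolled, but it does not threaten the main comparison.

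**What to change.** 1. Reconcile the Inclusion criteria and the Additional Objectives paragraph to a single MMSE threshold, and apply it identically to patients and spouse controls.
2. Use one delirium and dementia screen for both groups, and state whether a positive result excludes the person or is only recorded.
3. If people at 23-24 remain eligible, reword the label of significant impairment so that it no longer covers them, or say how they are handled in the comparisons.
4. Adjust the patient-control comparison for baseline MMSE. This can be specified in the analysis plan; it supports the common threshold and does not replace it.

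The cost is a few lines of protocol text. MMSE is already measured pre-operatively in patients, so the only extra data are the same baseline score in the 50 spouses. Keeping the existing patient threshold for both groups would lose no patient; the downside is a few controls with lower baseline scores.

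### Eligibility starts at 60 but the age strata for randomisation start at 65 and have no boundary rule, so eligible patients aged 60–64 have no list

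*Protocol*

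**What the plan says.** Four statements in the protocol bear on the age range.

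- **Section 8, participants:** "One hundred patients, 60 years of age and older".
- **Section 8, inclusion criterion 1:** "Patients over 60 years of age classified as ASA (American Society of Anesthesiologists) of three or less". Read strictly, this differs slightly from the participants sentence at age 60 itself.
- **Section 8, Randomisation:** the lists are "stratified by age group (65 to 70, 70 to 75 and over 75". The study statistician is to generate them in R. Sealed envelopes based on them go to the operating theatres and are opened only after eligibility and willingness have been confirmed again.
- **Section 2, Research objectives:** the frequency and importance of POCD are to be determined "in older people (over the age of 65".

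The closing paragraph of section 6 gives another age, saying the proposal will "clarify the full importance of POCD in people over the age of 70". That sentence describes the proposal's aim and is not an eligibility rule.

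None of the exclusion criteria for the randomised trial refers to age.

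**The concern.** Stratified randomisation works only if every eligible patient belongs to exactly one stratum. Here the same section sets both the eligibility limit and the strata, and the two do not fit together. A patient of 62 who meets every criterion and consents reaches theatre with no list from which to be allocated. Staff must then improvise a stratum or turn away an eligible patient, and either departs from the written plan.

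The boundaries raise a smaller problem of the same kind. Without a convention, two people applying the text in good faith could place the same patient in different lists.

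Two things are at stake: whether the allocation rule can be carried out as written, and whether the age balance that stratification is meant to secure is delivered. Because the objectives, the inclusion criterion and the strata do not share a lower limit, the reader cannot tell which one is in error.

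**Working it through.** There is no plan figure to reproduce. The check assigns each age to the stated strata.

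**Inputs (protocol section 8):** eligible at 60 and older (participants sentence) or over 60 (criterion 1); strata 65–70, 70–75 and >75.

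**Two readings, with age a in completed years:**

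- Closed intervals: 65 ≤ a ≤ 70; 70 ≤ a ≤ 75; a > 75.
- Half-open intervals: 65 ≤ a < 70; 70 ≤ a < 75; a > 75.

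| Age | Closed | Half-open |
|---|---|---|
| 60–64 | none | none |
| 65–69 | 65–70 | 65–70 |
| 70 | 65–70 and 70–75 | 70–75 |
| 71–74 | 70–75 | 70–75 |
| 75 | 70–75 | none |
| 76 and over | >75 | >75 |

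**Results**

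1. Ages 60–64 have no stratum under either reading. Taking criterion 1 strictly in completed years removes only age 60 from the gap and leaves 61–64.
2. The closed reading has one overlap, at 70. The half-open reading removes it but leaves 75 without a stratum. Neither gives each age from 65 upwards exactly one stratum.
3. If age is instead taken exactly, as time since birth, the shared endpoints are ordinary notation. The ambiguity then shrinks to the 70th birthday (closed) or the 75th birthday (half-open). The gap below 65 is unchanged.

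**Number affected.** If p is the share of enrolled patients aged 60–64, then 100 × p of the planned 100 patients have no list, or one patient for each percentage point. The protocol gives no value for p. The nearest age figure is the mean of 65 in the 46 retrospective abdominal cases in section 5. It comes without a spread and from a different sample, so it cannot be turned into a share aged 60–64.

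**The case against.** **This is a drafting slip that the statistician will repair.** Whoever generates the lists could treat the lowest stratum as everyone up to 70, and the trial is described as a pilot. The repair is indeed easy. But the text does not make it, and the protocol itself fixes both the eligibility age and the strata, so this is not a detail left to an analysis plan. The stated objective of over 65 makes a different repair, raising the age limit, equally plausible.

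**Allocation is not shown to be biased.** A reader might infer that unclear strata let the anaesthetist steer treatment. The documents do not support that. The envelopes are sealed and opened after eligibility is re-confirmed. Choosing between two lists would influence treatment only if the next code in each were known, and no route to that knowledge appears. Randomisation within whichever list is used still gives a valid comparison. This objection stands.

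**Three other stronger readings also fail.**

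- A reader might count patients aged 70 among those without a list. They are not: on the closed reading they have two lists, and on the half-open reading one.
- A reader might hold that ages 70 and 75 are both doubly covered. No single convention does this. In completed years age 75 is never in the top stratum, because that stratum begins above 75.
- A reader might use the 3-month POCD rates in section 3 (7% at 60–69, 14% at 70 and over) to measure the harm of the missing stratum. Those rates divide patients at 70 and say nothing about 60–64 against 65–69.

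**Conclusion.** The inconsistency is real and lies within section 8. Patients aged 60–64 are eligible but have no randomisation list under any reading, and nothing elsewhere in the protocol supplies one. The missing boundary convention is a second, smaller defect, affecting age 70 or age 75 depending on the reading. The objectives' limit of over 65 also disagrees with the eligibility age. It does not govern allocation, but it leaves the intended limit open. The over-70 wording in section 6 is weak evidence and the conclusion does not depend on it.

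The number of patients affected cannot be computed from the document. The demonstrated consequence is an allocation rule that cannot be executed for part of the eligible population, with loss of the intended age balance if strata are improvised. Neither bias nor loss of power has been shown. The conclusion rests only on the eligibility and stratification text as written.

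**What to change.** Before the lists are generated:

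1. Decide on the intended lower age limit and use it consistently in the participants sentence, inclusion criterion 1, the research objectives and the strata. The documents do not settle which limit is meant.
2. Define strata in completed years, at a stated reference date, that cover every eligible age exactly once. One way is to extend the lowest stratum down to the eligibility limit and assign ages 70 and 75 to one stratum each. If 65 is the intended limit, align the inclusion criterion with the strata and still settle the boundaries at 70 and 75.
3. Bring the age in the closing paragraph of section 6 into line for consistency.

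The cost is a short amendment of a few sentences. The protocol speaks of the lists as still to be generated; on that footing nothing has to be redone. Once enrolment has begun, patients allocated under improvised strata cannot be allocated again.
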